## Methods

### Overview

This implementation science study evaluates an adapted peer-support/lay-health intervention to increase HPV testing among WLWH and examines implementation, clinical outcomes, and sustainability metrics.

Our implementation process for the adapted MoMent HIV+HCC intervention involves: 1) facilitating SD conferences to collect input on how to adapt the MoMent program for CC control activities; 2) creating and implementing the HIV+ HCC intervention for the MoMent program; 3) measuring reach, adoption and implementation metrics at 6-month after intervention commencement; and 4) measuring intervention maintenance 18 months after intervention commencement. At the time of submitting this protocol, SD conferences were held and the intervention is adapted. We will conduct intervention activities through connections with clinics and existing MoMent programs across 15 clinics in eight Nigerian states.

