**FIGURE 1 F1:**
[figure not shown]
Aim 2 implementation flow chart (CHESS: Community, Home-based Education, Screening Services, Nigeria, 2025).

We will implement the adapted MoMent HIV+HCC program in 15 Nigerian clinical sites to recruit 30 MMs and 1500 WLWH for mid- and post-implementation assessments of reach, effectiveness, adoption, and fidelity. Implementation outcomes will be evaluated 6 months post-implementation with mixed methods. Key outcomes include reach and effectiveness, as indicated by eligible women touched by the HIV+HCC intervention, uptake of screening, women with high-risk HPV (hrHPV) 16/18/45/other genotypes treated, persistent or recurrent hrHPV post-treatment, and correlation of disease persistence with CD4 count and HIV viral load. We will measure program adoption outcomes that include training of MMs, WLWH who return a SC sample, and participating clinics’ integration of MoMent HIV+HCC into routine practice. We will gauge implementation fidelity as indicated by peer leaders’ progress reports. We will also measure system barriers and added cost of CC screenings.

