#### Recruitment of WLWH

We will recruit 1500 consenting WLWH from 15 healthcare facilities (100 per facility) across eight states over a period of 18 months. A sampling frame of WLWH will be generated using a report run by the clinic staff of eligible women currently receiving care. Eligible WLWH will be contacted via telephone by the MM who will provide information about the study process. WLWH who are interested in participating will be invited to a community education meeting. Upon arrival at the community meeting, the MM will educate about HPV screening, enroll interested participants into the study and facilitate logistics for the self-screening process in a private location at the meeting site.

Eligibility inclusion criteria include:Female genderDiagnosed with HIV and receiving care at study clinicAges 25–50yAble to consent to the study

The decision to screen WLHIV age 25–50 years is based on WHO recommendation which recommends HPV screening from age 25 years up to 65 years when there are tools to manage such women. However, we chose to limit our screening to upper age of 50 years because neither VIA nor ablative treatment, which are our proposed triaging test and first line treatments respectively, are suitable for women in whom the transformation zone is not visible which is typical after menopause. WLWH will not be eligible if they are pregnant, have had a hysterectomy or are not able/willing to perform vaginal self-collection.

A sample size of 1500 WLWH was determined after considering a design effect of 1.2 (to adjust for cluster sampling) and then incorporating a dropout rate of 20%. A sample size of 1500 has 89% power to detect an absolute difference in proportions of 0.04 using a two -sided exact test with a significance level of 0.05. This calculation assumes that the population proportion under the null hypothesis (P0) is 0.79. This is based on previous research that identified the proportion of women that are willing to screen for CC [33, 34].

Each week, MMs will call eligible patients and invite them to a culturally appropriate education session on HPV screening and SC. The MM will also introduce the CHESS study and take names for women who are interested in enrolling.

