To measure system flow, we will conduct rapid ethnography at a subset of 6 clinics (one per state) to assess daily clinical processes, recording observations in field notes. We will also follow 80 WLWH (10 per clinic) through the process, timing each step and noting barriers. Additionally, we will conduct virtual in-depth interviews (IDIs) with a clinical champion at each clinic (n = 15) and two focus groups (total n = 10–12) with HIV+HCC MMs to identify implementation barriers and facilitators. We will focus on MMs, who understand both systemic issues and the individual experiences of WLWH. Clinic champions will be asked to gather input from other staff before the IDIs to inform responses. Stakeholders will be informed they will participate in follow-up qualitative data collection at 18 months (Aim 3). IDIs and focus groups will be audio-recorded and transcribed, with a team member taking notes. Preliminary thematic analysis will be conducted to identify key barriers and facilitators to inform project adjustments.

Finally, we will capture project costs of adding the HCC components into the MoMent program as considerations for maintenance and sustainability. Measures will include costs for labor (clinical and laboratory staff and MMs), training and education, and clinical materials and supplies related to screening (e.g., Evalyn brush, GeneXpert Cartridge) and diagnosis (VIA consumables). Integrated findings will inform program refinement and support recommendations for scale-up and sustainability.

Aim 3Conduct post-implementation process evaluation of barriers and enablers to program maintenance.

In the maintenance phase, we will evaluate how the intervention has become routine practice at 18 months post-implementation. We will again collect data from the same stakeholders identified for Aim 2. Stakeholders’ viewpoints and processes related to the RE-AIM construct of “maintenance” will be assessed via quantitative measures (Table 1), structured interviews (n = 15), focus groups (n = 10–12), and numbers of WLWH screened/treated during the maintenance period. Stakeholders will also identify barriers to maintenance, resources available to support and capacity to scale the intervention across Nigeria.

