### Study Timelines

Broadly, our timeline follows the three study aims (Table 2): Aim 1 consists of the SD conferences and intervention adaptation which occurred in the first 18 months of the grant. Aim 2, which covers the implementation of the adapted intervention and six-month post intervention assessment, will happen in years 3–4. Aim 3, which includes the 18-month maintenance evaluation, will happen in years 4-5.

**TABLE 2 T2:** Study implementation timeline across project years. (CHESS: Community, Home-based Education, Screening Services, Protocol, Nigeria, 2022–2025).

Aim/Activity	Year 1		Year 2		Year 3		Year 4		Year 5	
**Aim 1:** Stakeholder Deliberations										
Development of SD process & data collection materials	X									
Recruitment of participants	X									
Hold SD conferences & analyze data	X	X								
Adapt HIV+HCC intervention		X	X							
Train clinic staff & peer support leaders to implement intervention		X	X							
**Aim 2:** Intervention Implementation & Evaluation										
Development of aim 2 data collection tools		X	X							
Implement HIV+HCC intervention				X	X	X	X	X		
Six-month post-implementation assessment data collection					X	X				
Six-month post-implementation assessment analysis						X				
Make necessary adaptations to HIV+ HCC intervention						X				
**Aim 3:** Post-Implementation Evaluation of Maintenance										
Development of aim 3 data collection tools							X			
18-month maintenance assessment data collection								X		
18-month maintenance assessment analysis								X	X	
Stakeholder dissemination									X	
Writing, presentations, publications									X	X

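### The 18-month maintenance assessment has two stated time origins; on the one that fits the timetable it falls within implementation, so it cannot show that the programme lasts beyond it

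*Protocol article*

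**What the plan says.** The protocol article gives two time origins for the same assessments.

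- **Methods, Overview:** "measuring reach, adoption and implementation metrics at 6-month after intervention commencement" and "measuring intervention maintenance 18 months after intervention commencement".
- **Aim 2 (text with Figure 1):** "Implementation outcomes will be evaluated 6 months post-implementation with mixed methods". The RE-AIM evaluation section also calls the six-month assessment post-implementation.
- **Aim 3 (end of the RE-AIM evaluation section):** "we will evaluate how the intervention has become routine practice at 18 months post-implementation". One of its measures is "numbers of WLWH screened/treated during the maintenance period". No start or end is given for that period.

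The calendar comes from three other places.

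- **Table 2:** the row "Implement HIV+HCC intervention" is marked from the second half of year 2 to the second half of year 4. The row "18-month maintenance assessment data collection" is marked only in the second half of year 4. Later columns hold analysis, dissemination and writing.
- **Study Timelines, text:** Aim 2 is placed in years 3 to 4 and Aim 3 in years 4 to 5.
- **Recruitment of WLWH:** 1,500 women are to be recruited "across eight states over a period of 18 months".

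At 18 months Table 1 lists as maintenance measures the ratio of patients to Mentor Mothers, refresher training and the test-to-treatment window.

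**The concern.** Aim 3 is meant to inform whether the adapted programme has settled into routine practice and can be scaled up. That requires a reader to know from which date 18 months is counted, and whether delivery by the study had stopped by then. The article leaves the first ambiguous and does not state the second.

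If the assessment falls while implementation is still running, some of what it records is the study's own activity. Under Recruitment of WLWH, a random draw of 10 women per month decides who enters the self-collection pathway, and interested women who are not drawn are offered VIA. While that holds, self-collection volume reflects study allocation. Staffing is set at two Mentor Mothers per 100 women at each site, so the 18-month ratio may partly reflect study staffing as well. The findings are to go into policy briefs and recommendations for scale-up, so the maintenance claim should match what is measured.

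**Working it through.** **Inputs.** Table 2 has two columns per project year, so column *k* covers project months 6(*k* − 1) to 6*k*.

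| Table 2 row | Columns marked | Project months |
|---|---|---|
| Implementation | 4 to 8 | 18 to 48 |
| Six-month data collection | 5 and 6 | 24 to 36 |
| 18-month data collection | 8 | 42 to 48 |

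The timeline ends at month 60.

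**Step 1: which time origin reproduces Table 2?**

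*Commencement.* The first marked column is 4, so the start lies between months 18 and 24.
- Six-month assessment: 18 + 6 = 24 to 24 + 6 = 30, inside the Table 2 slot of 24 to 36.
- 18-month assessment: 18 + 18 = 36 to 24 + 18 = 42. This meets the slot of 42 to 48 only if the start is at about month 24.

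*End of implementation.* The last marked column is 8, so the earliest possible end is month 42.
- Six-month assessment: 42 + 6 = 48 at the earliest, after its slot has closed at month 36.
- 18-month assessment: 42 + 18 = 60 at the earliest, which is the end of the timeline and after its slot has closed at month 48.

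Only the commencement origin fits.

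**Step 2: the Aim 2 start.** The text puts Aim 2 in years 3 to 4, so from month 24. Table 2 starts implementation between months 18 and 24. The choice changes what the slot means:
- start at month 24: the slot is 42 − 24 = 18 to 48 − 24 = 24 months after commencement;
- start at month 18: the slot is 42 − 18 = 24 to 48 − 18 = 30 months after commencement, which is no longer an 18-month assessment.

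**Step 3: position relative to recruitment.** Recruitment of 18 months from commencement ends at 18 + 18 = 36 to 24 + 18 = 42. An assessment at exactly 18 months falls due at the same moment, whatever the start. No interval then separates the end of enrolment from the maintenance readout.

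**Step 4: position relative to implementation.** The maintenance slot (42 to 48) lies wholly inside the implementation row (18 to 48). No programme assessment is marked in columns 9 or 10. The HPV retests of treated women at one and two years are clinical outcomes and do not measure whether clinics keep running the programme.

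**Step 5: the count.** Numbers screened or treated are to be totalled over a maintenance period with no boundaries. Since implementation continues through month 48, nothing in the article separates this total from the implementation total.

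**The case against.** The strongest reply is that the two origins are loose wording and not two schedules. Table 2 itself labels the six-month assessment post-implementation while placing it inside the implementation row, and follows it with adaptations to a programme that is still running. The term therefore seems to mean after launch. This stands. A reader might infer that the maintenance assessment is due only after the project has ended, but Table 2 rules out the end-of-implementation origin on which that inference depends.

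A reader might also infer that the study is still enrolling when maintenance is read. Table 2 does not show this: 18 months of recruitment closes at month 36 to 42, before or at the opening of the slot. The stated pace of 10 women per site per month would fill a site of 100 in 100 / 10 = 10 months, which is earlier still and does not match the stated 18 months. So the monthly limit cannot be said to fix the later counts. What remains is that an exact 18-month readout coincides with the end of the stated recruitment period, and that the slot overlaps the implementation row.

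A third tempting reading is that routine practice goes wholly unobserved. That is too strong. Table 1 measures staffing ratio, refresher training and treatment window at 18 months, interviews and focus groups are added, and Aim 3 is framed as a process evaluation of barriers and enablers. The Mentor Mothers are drawn from existing facility staff, and the article does not say when study support ends. Hence the result may overstate sustainability; the documents do not establish that it will.

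Finally, a full protocol might define the maintenance period. That would answer the missing dates, but not the conflicting wording and calendar in this article.

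**Conclusion.** The point holds in a limited form. The article states two time origins, and only commencement is compatible with its own timetable. On that origin the 18-month readout has zero months between the end of the stated recruitment period and the assessment. The sole maintenance data collection overlaps completely with the last six months of implementation, and no programme assessment follows.

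Aim 3 can therefore describe whether the running programme persists at 18 months. It cannot show persistence beyond implementation, and the screened-or-treated count cannot be told apart from study delivery. The stated Aim 2 start differs by up to six months between text and table, which moves the Table 2 slot from 18–24 to 24–30 months after commencement.

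This rests on reading Table 2 columns as half-years, on recruitment starting with implementation, and on recruitment lasting the stated 18 months. The size of any overstatement cannot be calculated, because the article does not say when study support stops.

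**What to change.** 1. Use one time origin, commencement, defined for example as each site's first enrolment, in the Overview, the Aim 2 and Aim 3 text, the RE-AIM evaluation section, Study Timelines and both tables.
2. Reconcile the Aim 2 start: years 3 to 4 in the text, second half of year 2 in Table 2. If the first column is the soft roll-out mentioned under Study Aims, say so.
3. Define the maintenance period as starting when a site's study enrolment closes, and give its end. Count women screened or treated in that period separately from study enrolees.
4. If enrolment runs the full 18 months, report the 18-month result as late implementation. Do not conclude that the programme has become routine practice or is sustained after implementation.

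The cost is mainly wording, plus a separate tally from clinic records, which are already a data source. No additional participants are needed. The downside is a weaker maintenance claim.

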### Study Timelines

Broadly, our timeline follows the three study aims (Table 2): Aim 1 consists of the SD conferences and intervention adaptation which occurred in the first 18 months of the grant. Aim 2, which covers the implementation of the adapted intervention and six-month post intervention assessment, will happen in years 3–4. Aim 3, which includes the 18-month maintenance evaluation, will happen in years 4-5.

**TABLE 2 T2:** Study implementation timeline across project years. (CHESS: Community, Home-based Education, Screening Services, Protocol, Nigeria, 2022–2025).

Aim/Activity	Year 1		Year 2		Year 3		Year 4		Year 5	
**Aim 1:** Stakeholder Deliberations										
Development of SD process & data collection materials	X									
Recruitment of participants	X									
Hold SD conferences & analyze data	X	X								
Adapt HIV+HCC intervention		X	X							
Train clinic staff & peer support leaders to implement intervention		X	X							
**Aim 2:** Intervention Implementation & Evaluation										
Development of aim 2 data collection tools		X	X							
Implement HIV+HCC intervention				X	X	X	X	X		
Six-month post-implementation assessment data collection					X	X				
Six-month post-implementation assessment analysis						X				
Make necessary adaptations to HIV+ HCC intervention						X				
**Aim 3:** Post-Implementation Evaluation of Maintenance										
Development of aim 3 data collection tools							X			
18-month maintenance assessment data collection								X		
18-month maintenance assessment analysis								X	X	
Stakeholder dissemination									X	
Writing, presentations, publications									X	X

## Results

Project results will be shared with researchers, practitioners, and policymakers. Aggregate findings will be disseminated to MMs, the project team, healthcare providers, hospital administrators, NGO stakeholders, academics, government officials, media, and funders. Channels will include MM trainings, seminars, conferences, policy briefs, letters to the editor, peer-reviewed journals, social media, and career platforms. Dissemination will address implementation processes, facilitators, barriers, strategies, and outcomes to enhance cervical cancer screening uptake and scale-up for women living with HIV, leveraging MM expertise.

A dissemination team—including project members, MMs, WLWH, and other stakeholders—will share information through meetings, digital platforms, and media. Efforts will be tailored by audience, considering language, interests, and purpose. Policymakers at local, state, and federal levels will receive policy briefs to support scaling cervical cancer screening in Nigeria. Principal investigators will evaluate dissemination to assess success and impact. The goal is to implement locally appropriate strategies that improve care quality and outcomes for WLWH in an LMIC setting.

### Limitations

This study is conducted in Nigeria and may have limited generalizability to other LMICs with different health system structures, sociocultural norms, and policy environments. Implementation challenges such as resource limitations, variability in MM training, and infrastructure constraints may affect program scalability and sustainability. Additionally, the reliance on self-reported data and clinic records may introduce reporting bias or incomplete outcome capture.

## Discussion

Nigeria has planned future resource allocation toward CC control and treatment [36], which were historically covered by non-governmental organization funds. This expansion of federal funds will allow for significantly expanded CC screening and treatment of WLWH nationwide.

Within this context and building upon the success of peer-support programs such as MoMent, our study will show the best approach to delivering a CC self-screening and treatment program in Nigeria for WLWH. This study also has the potential to expand equitable access to CC screening in LMICs beyond Nigeria.
